### Outcomes

The primary outcome is gestational age at birth, measured in days, based on the ultrasound assessment at the enrolment visit. Secondary outcomes are preterm birth (<37 completed weeks of gestation), low birth weight (birth weight <2500 g), miscarriage (dead fetus delivered before 28 completed weeks of pregnancy or with birth weight below 1000 g) and stillbirth (dead fetus delivered at or after 28 completed weeks of pregnancy or with birth weight above 1000 g).^33 34^ We chose gestational age at birth as the primary outcome because, while the cut-off of 37 weeks is the standard definition of preterm birth, dichotomisation of a continuous variable results in a loss of statistical power.^35^

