### Sample size calculation

The sample size has been calculated for objective 1, with a univariable comparison between the presence of a genital tract microorganism in the mother and gestational age at birth. Figure 2 shows that, for any vaginal or sexually transmitted microorganism, or vaginal microbiota type that has a prevalence of 10% or more among all enrolled women, about 500–600 patients provide adequate power (80%) to detect a 1-week difference (with SD 2) in mean gestational age between the two groups using Student’s t-test. Specifying an alpha of 0.83% allows for multiple hypothesis testing (six hypotheses, using a Bonferroni correction). We enrol around 600 women and aim to have complete follow-up and outcome data on at least 550 women.

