#### Objective 1: association between specified exposures and pregnancy outcomes

We will examine a primary set of microorganisms as exposures, detected at either enrolment or at the third trimester visit: *M. genitalium, M. hominis*, *U. urealyticum, U. parvum, T. vaginalis* and *Candida* spp are the microorganisms for which women did not receive diagnostic tests and treatment during study visits. We will use the mean and SD for the continuous outcome (gestational age) and absolute and relative frequencies for the binary outcomes (all secondary outcomes). Gestational age at birth for each exposure will be compared using Student’s t-test and a mean difference with 95% CIs (continuous outcome) and Fisher’s exact test and a risk difference with 95% CIs (binary outcomes).To control for confounding, multivariable regression models will be fitted to all outcomes with a set of prespecified potential confounders (age, educational level, alcohol consumption, HIV infection, prior preterm birth) for all organisms. For analyses of *M. genitalium*, *T. vaginalis* and *Candida* spp, we will also control for bacterial vaginosis (Nugent score 7–10). The other genital mycoplasmas can be identified from 16S rRNA amplicon sequencing in women with vaginal dysbiosis, so are sometimes considered part of bacterial vaginosis. For these organisms, we will conduct descriptive analyses, stratified by the presence of bacterial vaginosis. For continuous confounders, a linear relationship will be assumed by default but transformations (eg, log) or more flexible approaches (eg, splines or fractional polynomials) will be considered if there is evidence for non-linearity. For the continuous outcome, we will use linear mixed-effects regression models (including data from either visit and the participant as random effect) and report the result as mean difference with 95% CIs. For the binary outcome, we will use logistic mixed-effects regression and report the result as ORs with 95% CIs.Comparisons for associations with timing of detection, other microorganism exposures and birth outcomes will be considered secondary analyses. Associations between vaginal microbiota composition and pregnancy outcomes will be assessed. We will use compositional multivariable analysis methods to identify bacterial taxa that are differentially abundant between binary pregnancy outcome groups at the level of individual taxon relative abundances. We will use mixed-effects models (with the individual participant as the random effect and including data from both visits) to assess associations between continuous and binary pregnancy outcome and the following fixed effects derived from the vaginal microbiota data: alpha diversity, vaginal microbiota types and absolute abundances of predefined bacterial groups.^46^ These models will be adjusted for confounding as described in the previous paragraph.

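### The full adjusted logistic model is fixed for every outcome, including miscarriage and stillbirth, where events may be too few to give stable or estimable odds ratios

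*Protocol article*

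**What the plan says.** Under Objective 1 in the Statistical analysis section, the protocol article says that "multivariable regression models will be fitted to all outcomes with a set of prespecified potential confounders". The set is listed as "age, educational level, alcohol consumption, HIV infection, prior preterm birth) for all organisms". For *M. genitalium*, *T. vaginalis* and *Candida* spp it adds: "we will also control for bacterial vaginosis (Nugent score 7–10". The model type is also fixed: "For the binary outcome, we will use logistic mixed-effects regression and report the result as ORs with 95% CIs".

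The Outcomes section lists four binary secondary outcomes: preterm birth, low birth weight, miscarriage and stillbirth. Miscarriage is defined as "miscarriage (dead fetus delivered before 28 completed weeks of pregnancy or with birth weight below 1000 g", and stillbirth by the complementary limits. No expected rate is given for either.

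Before any adjustment, binary outcomes are compared by "Fisher’s exact test and a risk difference with 95% CIs (binary outcomes". On numbers, the Sample size calculation section says "We enrol around 600 women and aim to have complete follow-up and outcome data on at least 550 women". That calculation covers only the univariable comparison of mean gestational age.

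The article states no minimum event count, reduced covariate set, penalised method or descriptive-only rule for rare outcomes.

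**The concern.** A logistic model is limited by the number of events, not the number of women. With few events per coefficient, maximum-likelihood log odds ratios tend to lie too far from zero. If no exposed woman has the event, the exposure odds ratio has no finite estimate (it runs to zero). The same happens to any covariate that separates events from non-events.

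The two visits do not help. A woman sampled twice still has one pregnancy outcome, so a second record adds no event.

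The article's rule would produce 12 adjusted odds ratios for these two outcomes (six organisms × two outcomes). If some models failed, the analyst would have to drop covariates or change method after seeing the data, and readers could not tell which choices were planned.

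**Working it through.** **The plan's own figure.** The sample size reproduces. For a 1-week difference, SD 2, 10% exposed, 80% power and two-sided alpha 0.83%, the normal approximation gives 485 unexposed, and 485 / 0.9 = 539 in total. The exact t-test gives 543. The article says about 500–600. This says nothing about binary outcomes.

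**Inputs.**
- Women with outcome data: 550 (Sample size calculation).
- Coefficients, not counting the intercept and random-effect variance: 1 exposure + 5 confounders = 6, or 7 with bacterial vaginosis (Objective 1). This is a minimum, because multi-level education or alcohol, or the non-linear terms the article allows, would add more.
- Preterm birth rate: about 10% (Introduction).
- Miscarriage and stillbirth rates: not in the article; 1–4% each is assumed.
- Organism prevalence: not in the article. The sample size section uses 10% or more as a condition for power. Both 10% and 30% are shown here as assumptions.

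**Events per coefficient** = 550 × rate / number of coefficients.

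| Rate | Events | Per coefficient (6) | Per coefficient (7) |
|---|---|---|---|
| 1% (assumed) | 5.5 | 0.9 | 0.8 |
| 2% (assumed) | 11 | 1.8 | 1.6 |
| 3% (assumed) | 16.5 | 2.8 | 2.4 |
| 4% (assumed) | 22 | 3.7 | 3.1 |
| 10% (preterm birth) | 55 | 9.2 | 7.9 |

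Turned round, 5 events per coefficient needs 5 × 6 = 30 to 5 × 7 = 35 events. That is 30/550 = 5.5% to 35/550 = 6.4% for each outcome separately.

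**Chance that no exposed woman has the event**, with no true effect = (1 − exposure prevalence)^events.

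| Events | 10% exposed | 30% exposed |
|---|---|---|
| 6 | 0.9^6 = 53% | 0.7^6 = 12% |
| 11 | 0.9^11 = 31% | 0.7^11 = 2% |
| 16 | 0.9^16 = 19% | 0.7^16 = 0.3% |
| 22 | 0.9^22 = 10% | 0.7^22 = 0.04% |

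**Simulation, for direction only.** There were 1000 ordinary logistic fits per scenario, with 550 women, 7 coefficients, a true exposure odds ratio of 1.7 (log 0.53), and assumed covariate prevalences and effects.
- At 10% exposure, the exposure odds ratio was not estimable in 42%, 17% and 8% of fits at event rates of 1%, 2% and 3%. Some coefficient was infinite in 73%, 32% and 15%.
- At 30% exposure, the exposure odds ratio was not estimable in 14%, 1.7% and 0.1%.
- At 10% exposure, the mean finite log odds ratio was 1.19, 0.67 and 0.50. At 30% exposure it was 0.66, 0.53 and 0.48. Part of the excess at the 1% rate is selection, because only fits with a finite estimate are averaged.
- At a 10% event rate no separation occurred.

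**The case against.** The article calls its statistical section an overview and defers to a separate analysis plan. A sparse-data fallback is the kind of detail such a plan usually holds, and a default adjustment set does not forbid one. This has weight, and the missing fallback alone would be no finding. But the article goes further than silence: it applies one covariate set and one model type to all outcomes. An analysis plan that follows that text inherits the problem.

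A reader might also infer that the adjusted odds ratios for these outcomes will be biased or infinite. The article does not support that. It gives neither event rates nor organism prevalences, and the result depends on both. At 30% exposure and event rates of 2–3%, the simulated exposure odds ratio was nearly always estimable and its mean was close to the truth. What can be said is that the estimates may be unstable or may not exist.

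Three further points stand. Only secondary outcomes in a hypothesis-generating study are affected. The Fisher's exact test and risk difference already planned remain usable. And cutting confounders from an observational analysis to gain stability exchanges one bias for another, so a smaller model is not plainly better.

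**Conclusion.** The point holds in conditional form. The article commits the study to a 6–7 coefficient logistic model for miscarriage and stillbirth without a sparse-data safeguard. At assumed rates of 1–4% that means about 0.8–3.7 events per coefficient. Each outcome would need a rate of 5.5–6.4% to reach 5 per coefficient.

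The risk that the exposure odds ratio cannot be estimated is substantial for an organism at 10% prevalence (53% down to 10% over 6–22 events, with no true effect). It is small for one at 30% prevalence unless events are very few (12% down to under 0.1%). Both the rates and the prevalences are assumptions.

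The primary outcome is continuous and is not affected. Preterm birth, at about 8–9 events per coefficient, is acceptable rather than generous. No low birth weight rate is given, so keeping the full model there assumes that it is not much rarer than preterm birth.

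**What to change.** In the analysis plan, for miscarriage and stillbirth only:
- Make the planned Fisher's exact test and crude risk difference the main result, with an exact confidence interval.
- Replace the ordinary logistic mixed model with a Firth-penalised logistic model, one record per pregnancy, with profile-likelihood confidence intervals, labelled exploratory.

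Keep the full maximum-likelihood model for preterm birth and low birth weight.

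A smaller covariate set, or a combined fetal-loss outcome, is optional. Either should be prespecified as a sensitivity analysis, because it gives up confounder control or outcome detail for stability.

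The cost is wording; no new data are needed. One record per pregnancy requires a single exposure status per woman, for which the article's own definition (detection at either visit) can serve. Penalised estimates will still have wide intervals when events are few, and the exploratory label should make that plain.

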### Participants

Inclusion criteria: Pregnant women aged 18 years or older, who live in Buffalo City Metropolitan Municipality, intend to deliver in the same municipality and provide written informed consent to take part in the study. The eligible gestational age at enrolment, confirmed by ultrasound, was below 20 weeks at the start of the study in March 2021 and was increased to 27 weeks in September 2021 to increase enrolment and to align with another trial.^29^

Exclusion criteria: Participation in any other research study or inability to understand and speak a local language (English, Afrikaans or isiXhosa).

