### Statistical analysis

This description gives an overview of the statistical methods for each objective. A detailed statistical analysis plan will be published separately and made publicly available.

We will describe the numbers of women enrolled and available at each follow-up visit in a flow chart. We will present descriptive tables of sociodemographic, behavioural and clinical characteristics and compare women with complete follow-up with those lost to follow-up.

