#### Objective 3: classification and regression tree analysis for the primary outcome

We will conduct exploratory analyses to examine the combination of microorganisms that best predicts earlier gestational age at birth using classification and regression tree analysis.^50^ This method belongs to the family of decision tree machine learning algorithms and allows for non-parametric analyses of a large number of binary, categorical or continuous predictors. They are typically easy to interpret and can detect predictors with small marginal effects when there are strong interaction effects. We will make use of the predictive potential for gestational age at birth of all sexually transmitted and genital tract microorganisms, including individual bacterial taxa or bacterial groups identified by 16S rRNA gene amplicon sequencing (as binary or continuous variables) and confounding variables identified in objective 1. We will present variable importance scores and curves of marginal effects to show how prediction of the outcome changes at different levels of the exposure of each variable in the model. To avoid overfitting, we will consider bootstrap aggregating via random forests.^51^

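### The fixed confounder list has prior preterm birth but not parity, so a plain yes/no coding cannot separate women with no previous birth from women with only term births

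*Protocol article*

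**What the plan says.** Under Objective 1, "multivariable regression models will be fitted to all outcomes", with a named set of "prespecified potential confounders (age, educational level, alcohol consumption, HIV infection, prior preterm birth) for all organisms". Bacterial vaginosis is added for three of the organisms. Neither parity nor gravidity appears in this list or anywhere else in the article.

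The list reaches beyond the organism-by-organism models:

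- For the vaginal microbiota models, still under Objective 1: "These models will be adjusted for confounding as described in the previous paragraph".
- Objective 2 adds infection results as covariates to those same regression models.
- Objective 3 feeds "confounding variables identified in objective 1" into the tree analysis.

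The Participants section admits "Pregnant women aged 18 years or older, who live in Buffalo City Metropolitan Municipality, intend to deliver in the same municipality" and who consent, subject to a gestational-age limit. The exclusions are "Participation in any other research study or inability to understand and speak a local language". Neither part asks for a previous birth.

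The article does not give the levels of the prior-preterm-birth covariate and does not mention women without a previous birth. The Statistical analysis section calls itself an overview and adds: "A detailed statistical analysis plan will be published separately and made publicly available".

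**The concern.** Including prior preterm birth implies that obstetric history carries information about the length of the current pregnancy. A woman whose births were all at term has an informative history. A woman who has never given birth has none. A yes/no term gives both the same value.

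Age does not stand in for the missing distinction. It enters linearly by default. Even a flexible age curve cannot separate two women of the same age, one with term births and one with none.

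This is an observational cohort, so the adjusted models are its main protection against confounding, and the Introduction criticises earlier work for weak control of it. If women with no previous birth differ from parous women both in carriage of an organism and in gestational age, part of that difference would be attributed to the organism. Because one list serves several analyses, the same gap would recur in each.

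**Working it through.** **1. The plan's own figure.** Inputs from the Sample size calculation section: difference 1 week, SD 2 weeks, 10% exposed, power 80%, alpha 0.83% (0.05/6; two-sided is assumed, as the article does not say).

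N = [SD × (z for alpha + z for power)]² / [difference² × p(1 − p)]
= [2 × (2.6396 + 0.8416)]² / (0.10 × 0.90)
= 48.475 / 0.09 = 538.6, so 539.

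The exact t-test gives 543, and power at the target of 550 women with complete data is 80.7%. This agrees with the stated 500–600. The calculation uses no covariates, so the confounder list does not touch it. The same holds for the t-test and Fisher comparisons under Objective 1.

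**2. Eligibility against the covariate.** The criteria allow three kinds of women:

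| Obstetric history | Eligible? | Prior preterm birth as yes/no | Three-level covariate |
|---|---|---|---|
| No previous birth | yes | no | level 1 |
| Previous birth(s), none preterm | yes | no | level 2 |
| At least one previous preterm birth | yes | yes | level 3 |

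Under the yes/no coding the first two rows are identical. No coefficient in the model can take up a difference between them.

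**3. How many women share the level.** The article gives no parity figure. Assuming that 20% to 50% have had no previous birth, 550 × 0.20 = 110 to 550 × 0.50 = 275 women would sit in the reference level without a history to judge.

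**4. What that could do to an estimate.** In a linear model for gestational age, the shift in an organism's coefficient from omitting the distinction is g × d. Here g is the adjusted difference in gestational age between women with no previous birth and women with only term births. The term d is the difference between exposed and unexposed women in the share with no previous birth, given the other covariates. Neither is in the documents. For assumed values, in weeks:

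| g | d = 0.05 | d = 0.10 | d = 0.20 |
|---|---|---|---|
| 0.1 | 0.005 | 0.010 | 0.020 |
| 0.2 | 0.010 | 0.020 | 0.040 |
| 0.3 | 0.015 | 0.030 | 0.060 |
| 0.5 | 0.025 | 0.050 | 0.100 |

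The largest entry is a tenth of the 1-week difference used for the sample size. The sign is open, because g and d may each be positive or negative. If either is zero, nothing is left to remove.

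**5. After the change.** The three-level covariate is defined for every woman, so none is lost for lack of a previous birth and N stays at 550.

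**The case against.** The best defence is that the article states no coding at all. It names the covariate but does not call it binary, and a three-level version could be used without adding an item to the list. Levels of covariates commonly belong in the analysis plan, which is announced but not shown. The article also gives no levels for educational level, alcohol consumption or HIV infection. Nor does it supply evidence that parity is related to these organisms or to gestational age: the Introduction does not list it among the factors said to predispose to preterm birth.

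Much of this stands. The point depends on the plain yes/no reading, and confounding by parity is a possibility, not something shown.

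The defence does not remove the point. The choice of confounders is not deferred: the article publishes it as prespecified, and parity is not in it. Any separation of women with no previous birth therefore rests on how one covariate is coded, and the simplest reading of its name fails to provide it.

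**Conclusion.** The point holds as a specific, inexpensive improvement to the adjusted analyses. It does not show that a stated result or figure is wrong. It rests on two things: the eligibility criteria, which admit women in a first pregnancy, and a plain yes/no reading of prior preterm birth. The amount of residual confounding is unknown; the range of 0.005 to 0.10 weeks comes wholly from assumed inputs.

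Two stronger readings are tempting, and the documents support neither.

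- A reader might infer that women with no previous birth will be dropped from the adjusted models as not applicable. With 20% to 50% of 550 lost, 440 to 275 would remain, and univariable power at 10% exposed would fall from 80.7% to between 69% and 43%. The article describes no such code, no complete-case rule and no exclusion of these women, and the share is assumed.
- A reader might infer that every adjusted estimate is confounded by parity. That would require parity to be related to each organism and each outcome after the listed adjustment, and nothing in the article establishes this.

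**What to change.** In the statistical analysis plan, replace prior preterm birth with one obstetric-history covariate of three levels, used in all adjusted models and among the Objective 3 predictors:

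1. no previous birth;
2. previous birth(s), none preterm;
3. at least one previous preterm birth.

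State also which level applies to a woman whose earlier pregnancies all ended in miscarriage, so that every participant has exactly one level.

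The cost is a sentence of text and one extra parameter per model. New data should not be needed, since recording prior preterm birth presupposes asking about previous births; this should be checked against the case report forms, which are not shown. For gestational age with about 550 women the extra parameter is negligible. For binary outcomes with few events it weighs more, and the plan can say so.

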**Methods and analysis:**

This cohort study enrols around 600 pregnant women at one public healthcare facility in East London, South Africa. Eligible women are ≥18 years and at <27 weeks of gestation, confirmed by ultrasound. At enrolment and 30–34 weeks of pregnancy, participants receive on-site tests for *Chlamydia trachomatis* and *Neisseria gonorrhoeae*, with treatment if test results are positive. At these visits, additional vaginal specimens are taken for: PCR detection and quantification of *Trichomonas vaginalis*, *Candida* spp., *Mycoplasma genitalium, M. hominis*, *Ureaplasma urealyticum* and *U. parvum*; microscopy and Nugent scoring; and for 16S ribosomal RNA gene sequencing and quantification. Pregnancy outcomes are collected from a postnatal visit and birth registers. The primary outcome is gestational age at birth. Statistical analyses will explore associations between specific microorganisms and gestational age at birth. To explore the association with the quantity of microorganisms, we will construct an index of microorganism load and use mixed-effects regression models and classification and regression tree analysis to examine which combinations of microorganisms contribute to earlier gestational age at birth.

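### The prespecified adjustment set omits gestational age at enrolment although entry runs up to 27 weeks, which can bias the miscarriage comparison and, if early losses are counted, mean gestational age at birth

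*Protocol article*

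**What the plan says.** All references are to the protocol article.

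- **Adjustment (Objective 1).** For all organisms and all outcomes the confounders are "prespecified potential confounders (age, educational level, alcohol consumption, HIV infection, prior preterm birth". For *M. genitalium*, *T. vaginalis* and *Candida* the article adds that "we will also control for bacterial vaginosis (Nugent score 7–10" applies. Neither gestational age at enrolment nor enrolment period is named. The same set is carried into the microbiota models, and Objective 3 uses the confounders identified in Objective 1.
- **Entry (Participants; abstract).** The eligible gestational age "was below 20 weeks at the start of the study in March 2021 and was increased to 27 weeks in September 2021". The abstract gives the present rule: "Eligible women are ≥18 years and at <27 weeks of gestation, confirmed by ultrasound".
- **Outcomes.** "The primary outcome is gestational age at birth, measured in days, based on the ultrasound assessment at the enrolment visit". Miscarriage is a dead fetus before 28 completed weeks or under 1000 g. Stillbirth starts at 28 weeks or is above 1000 g. The other two secondary outcomes are "preterm birth (<37 completed weeks of gestation") and "low birth weight (birth weight <2500 g"). The article does not say whether losses before 28 weeks enter the mean of the primary outcome.
- **Tests (Objective 1).** Binary outcomes are compared by Fisher's exact test with a risk difference, then by logistic mixed-effects regression. Timing of detection is a secondary comparison.

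**The concern.** The enrolment visit fixes when a woman comes under observation, when her first swab is taken and how her pregnancy is dated. Losses before that visit cannot be seen. Two women with the same underlying risk of miscarriage therefore have different chances of contributing an event, depending only on when they enrolled. An analysis that ignores entry time is safe if entry time is unrelated to detection of the organism. If detection changes over pregnancy, or if women with an organism book earlier or later, exposed and unexposed women differ in time at risk, and the difference shows up as an association with miscarriage. If early losses also count as births at a very low gestational age, part of it passes into the primary outcome.

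Entry below 20 weeks was already delayed entry. The change in September 2021, about six months into recruitment, did not create the problem. It enlarged it by admitting women who have almost no time left in which to miscarry.

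**Working it through.** **1. The plan's own figure, as a yardstick.** Inputs from the sample size section: difference 1 week, SD 2, alpha 0.0083 (taken as two-sided), power 80%, exposure 10%.

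N = (z₁₋α/₂ + z₀.₈)² × SD² / [difference² × p(1 − p)] = 3.481² × 4 / 0.09 ≈ 539.

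The exact t calculation gives 543. The stated 500 to 600 reproduces, so this point does not touch the sample size. The 1-week difference is the scale for judging any bias in the primary outcome.

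**2. Time at risk of miscarriage.** On the gestational-age criterion it is 28 minus the week of entry: 28 − 9 = 19 weeks, 28 − 20 = 8 weeks, 28 − 26 = 2 weeks.

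**3. Bias with no true effect, by hand.** None of the following inputs is in the documents; all are assumptions:
- entry uniform over 8 to 27 weeks;
- a fraction L = 5% to 10% of pregnancies lost, spread evenly over weeks 8 to 28;
- births otherwise at mean 39 weeks;
- detection on the enrolment swab falling linearly from 25% (or 15%) at week 8 to 10% at week 27.

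Write u = entry week − 8, so u is uniform on 0 to 19, with E[u] = 9.5 and E[u²] = 361/3 = 120.33. Time at risk is 20 − u, with mean 10.5. Pregnancies that are not lost are equally frequent at every u, so the miscarriage odds ratio equals the ratio of mean time at risk, exposed to unexposed.

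- *Detection 25% to 10%.* p(u) = 0.25 − (0.15/19)u and E[p] = 0.175. E[(20 − u)p] = 5 − 2.375 − 1.5 + 0.95 = 2.075. Exposed: 2.075/0.175 = 11.86 weeks. Unexposed: (10.5 − 2.075)/0.825 = 10.21 weeks. Odds ratio = 11.86/10.21 = **1.16**.
- *Detection 15% to 10%.* E[p] = 0.125. E[(20 − u)p] = 3 − 1.425 − 0.5 + 0.317 = 1.392. Exposed: 11.13 weeks. Unexposed: 9.108/0.875 = 10.41 weeks. Odds ratio = **1.07**.
- *Detection rising 10% to 25%.* E[(20 − u)p] = 10.5 × 0.35 − 2.075 = 1.6. Exposed: 9.14 weeks. Unexposed: 8.9/0.825 = 10.79 weeks. Odds ratio = **0.85**; the sign has reversed.

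For mean gestational age with losses counted, a woman entering at u loses on average (L/20) × [(31 − u)² − 11²]/2 weeks. Averaged over exposed minus unexposed women, the bracketed half is 214.8 − 179.5 = 35.4 (detection 25% to 10%) or 199.3 − 183.7 = 15.6 (15% to 10%). Multiplying by L/20 = 0.0025 to 0.005 gives **-0.04 to -0.18 weeks**.

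**4. Simulation.** With the same inputs, and loss either even or concentrated early, the miscarriage odds ratio is 1.06 to 1.31 and the crude mean difference -0.03 to -0.19 weeks. The upper end of the odds ratio needs early-concentrated loss. Adjusting for entry week takes the mean difference to about zero. Stratifying by entry week gives odds ratios of 0.99 to 1.02.

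**5. Simulation with a true 1-week shift** (assumed: 10% exposed, 3% loss over weeks 12 to 28, entry from week 8 to 27).

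| Scenario | All pregnancies | Enrolled, crude | Enrolled, adjusted for entry | Miscarriage RR seen (true) | Live births |
|---|---|---|---|---|---|
| Entry unrelated to exposure | -0.98 | -0.99 | -0.99 | 1.02 (1.0) | -1.00 |
| Exposed enter later | about -0.97 | -0.85 | -0.99 | 0.58 (1.0) | -1.00 |
| Exposed enter later, exposure doubles loss | -1.59 | -1.01 | -1.15 | 1.15 (2.0) | -1.00 |

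The first row shows that no bias arises without a link between entry and exposure. The last row shows that the covariate alone recovers only part of the gap, because losses before entry stay unseen. Among live births nothing changes in any row.

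**6. Other outcomes.** Stillbirth begins at 28 weeks, after the latest entry. Low birth weight is defined by weight without dating. With mean 39 (assumed) and SD 2, a normal distribution puts about 1 in 10⁹ live births before 27 weeks. Real left tails are heavier, but such births are still few.

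**The case against.** The strongest reply has four parts.

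- **The bias is conditional.** It needs entry time to be related to detection, and the documents give no data on that. This stands: even the direction is unknown.
- **The figures do not model the planned exposure.** Objective 1 counts detection at either enrolment or the third-trimester visit, whose window is fixed at 30 to 34 weeks. The calculations use the enrolment swab only. This stands, so they show a mechanism and an order of magnitude and do not predict the planned comparison.
- **The primary outcome is barely moved.** A shift of 0.03 to 0.19 weeks is 0.2 to 1.3 days, or 3% to 19% of the 1-week design difference, and it appears only if early losses count. This stands.
- **The article is an overview and promises a separate analysis plan.** This disposes of any complaint that delayed-entry models are missing. It does not dispose of the list: the article names the confounders, calls them prespecified and applies them to all outcomes. The secondary comparison by timing of detection is not adjustment for entry time.

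A reader might infer two stronger points. The first is that truncation affects every outcome. Step 6 and the live-birth column show that it does not. The second is that late scans undermine the outcome because it is dated "based on the ultrasound assessment at the enrolment visit". The documents give no figure for dating error by gestation. Such error does not bias a mean difference unless it is systematic or linked to exposure, and the covariate would not remove it. Nor should the simulated odds ratios be set against the 1.3 to 2.0 cited in the Introduction, which concerns adverse birth outcomes generally.

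**Conclusion.** The omission is real and worth correcting, but its reach is narrow. It matters mainly for miscarriage, a secondary outcome. It reaches mean gestational age at birth only if losses before 28 weeks are counted; the same condition would apply to preterm birth.

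Under no true effect and the assumed inputs in steps 3 and 4, the miscarriage odds ratio is about 1.06 to 1.31 and the mean difference about -0.03 to -0.19 weeks. Both reverse in sign if detection rises with gestation. Both vanish if entry time and detection are unrelated. Live births, stillbirth and low birth weight are hardly affected, and the sample size stands.

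**What to change.** 1. Add gestational age at enrolment (linear or spline) to the prespecified adjustment set for all organisms and outcomes.
2. Analyse miscarriage on the gestational-age scale with delayed entry at enrolment, so that each woman counts as at risk only from the week she joined. The covariate alone does not fully correct truncation.
3. Add a sensitivity analysis restricted to women enrolled below 20 weeks, whichever side of September 2021 they joined.
4. State whether losses before 28 weeks are included in mean gestational age at birth, since the effect on the primary outcome depends on it.

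The cost is one to three degrees of freedom, some wording and a little extra analysis. No new data are needed, because gestational age is measured by ultrasound at enrolment for every participant. Miscarriages may be few, so a linear term may be all that model can carry. None of these steps corrects dating error in the scan, and they should not be presented as doing so.
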